#### Quantitative analysis

We will use univariate and bivariate statistics to determine the distribution of outcome measures and to identify relevant covariates (75). To test between-group differences in post-intervention MetS and positive youth development, intervention and delayed intervention control group districts will be evaluated using a generalized linear model framework, in which the treatment group (intervention vs. delayed intervention control group) will be the primary independent variable, baseline score as a covariate, post-intervention score is the outcome, and district is a clustering variable (76). Other covariates (e.g., student sex), identified in the preliminary bivariate analyses, will also be included in the model. If missing data occurs, we will mitigate potential biases and loss of statistical power by analyzing multiple imputed datasets under an intention-to-treat approach (77). These analyses will be compared to per-protocol analyses to allow for the assessment of intervention effects under different conditions (78).

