## Methods and analysis

### Design

We will recruit two cohorts of schools (*n* = 20 schools, total) to participate in a 9-month pilot cluster randomized controlled trial. The study design processes—including school recruitment, enrollment, and randomization, as well as student recruitment, data collection timepoint, and program participation—are illustrated in Figure 1 and described in detail below. Once a school agrees to participate, it will be randomized to receive the STHS intervention immediately or a delayed intervention condition (i.e., control group). The delayed intervention group will receive the curriculum to implement at their discretion, one school year after serving as a control. We will collect pre-(beginning of the academic year; T1) and post-test outcomes (end of the academic year; T2) for intervention and delayed intervention conditions. Additionally, for the intervention group, we will gather outcomes at 4 months (T3) and 12 months (T4) post-intervention to assess the short- and long-term maintenance of the intervention effects. The trial has been registered on clinicaltrials.gov (NCT05867433). The Institutional Review Board at Texas A&M University approved all measures, procedures, and protocols (IRB2023-0530D).

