#### Randomization

Randomization of schools into the immediate intervention or delayed intervention control conditions will be carried out by a statistician using an automated computer program. Randomization will occur in two blocks of ten schools, at an equal one-to-one ratio. The statistician will keep the resulting group assignments in a downloaded file and restrict file access from the study team. The research team will be blinded to randomization during the recruitment process. Once a school is committed to the study (i.e., signed MOU), the statistician will inform the study team to which group the school has been randomized. Each school will be randomized in the order in which they commit to participating in the study.

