### Data analysis

#### Sample size

As abdominal obesity is a necessary component of MetS, we powered this study on between-group changes in obesity. Based on the existing literature, we set an alpha of 0.05 and estimated a within-school intraclass correlation coefficient of 0.025 to account for cluster effect, an effect size of *d* = 0.27, and an effect size variability of 0.07. As a result, we will need to recruit 20 participants per school to achieve 80% power to detect a statistically significant change in abdominal obesity between the intervention and control group participants. Previous school- and community-based studies have shown similar effect sizes for changes in obesity-related outcomes (69–72). We will aim to recruit 25 students per school to ensure that we have 20 students available for measures, given that the normal retention rate is 80% in community-based research. We anticipate low participant attrition given that the school setting provides a controlled environment where consistent attendance is expected and buy-in from school administration and teachers often leads to higher student engagement and accountability (73). Furthermore, we will be working with Extension agents who often have strong community ties, fostering trust and rapport with students and families (74).

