This study is not without its limitations. First, the STHS program will be delivered in both public and private middle schools in a variety of settings with different policies and administrators. We have hired student implementers to minimize variation and measure curriculum fidelity, allowing us to identify significant deviations. The flexibility in delivering the curriculum, as discussed above, may introduce variability but only affects the frequency of delivery, not the learning objectives of each session. Second, the randomized design with a delayed intervention control group may present challenges for Extension agents or school staff. For example, if school staff planned to deliver STHS during school hours, but they were randomized to receive the delayed intervention control condition, they may seek to replace STHS with a similar program. Given the STHS program's unique approach, it is unlikely that a comparable program is available (i.e., a program that combines civic engagement with nutrition and physical activity education); however, they may choose a program that addresses one of the primary outcomes (e.g., positive youth development). Although we considered traditional non-contract control, school staff and Extension agents expressed ethical concerns with denying programming to community members. Therefore, the delayed intervention control condition was deemed the most appropriate.

Overall, this study will evaluate the efficacy of STHS in improving MetS and promoting positive youth development among middle school students. The findings will also provide evidence on whether STHS is effective in improving physical activity and nutrition outcomes at the individual, social, and environmental levels. If found to be effective, this will pave the way for larger-scale studies and inform efforts to disseminate STHS. The study addresses a critical gap in interventions for middle school students by concurrently emphasizing youth civic engagement, nutrition, and physical activity. By promoting student-driven initiatives and employing innovative methods like photovoice, the STHS program represents a significant advancement in health promotion for middle school students.

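### The primary model compares and clusters on districts, although schools are recruited and randomised; if several schools share a district, the type I error may exceed 5%

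*Protocol article*

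**What the plan says.** The Randomization section makes the school the unit of allocation: "Randomization of schools into the immediate intervention or delayed intervention control conditions will be carried out by a statistician". It adds that "Randomization will occur in two blocks of ten schools, at an equal one-to-one ratio", with each school allocated in the order in which it commits. The Design section gives the total as 20 schools. The Sample size section allows for clustering at the same level: "we set an alpha of 0.05 and estimated a within-school intraclass correlation coefficient of 0.025 to account for cluster effect".

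The Quantitative analysis section changes the unit. For the two primary outcomes, metabolic syndrome and positive youth development, "intervention and delayed intervention control group districts will be evaluated using a generalized linear model framework". In the same sentence the baseline score is a covariate, "post-intervention score is the outcome, and district is a clustering variable". School does not appear in that model.

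The limitations paragraph of the Discussion notes that "the STHS program will be delivered in both public and private middle schools".

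**The concern.** In a cluster randomised trial the analysis has to allow for correlation at the level that was randomised. Here that level is the school, and the stated model names another. This is not a detail left to a later analysis plan: the article names a clustering variable, and it conflicts with the article's own design and sample size.

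District is not a safe stand-in. No section recruits, counts or randomises districts. Allocation is not stratified by district, so two schools in one district can fall in different arms, and an intervention district may not exist as a category. How a private school would be assigned a district is not stated.

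At stake are the standard errors, confidence intervals and p-values of both primary comparisons. If several schools share a district and the model carries only a district random intercept, part of the school-level correlation is left in the residual, as if students from different schools in a district were exchangeable.

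**Working it through.** **Inputs from the article.** 20 schools, 1:1 in two blocks of ten; 20 students measured per school (25 recruited); school ICC 0.025; alpha 0.05, taken as two-sided because sidedness is not stated. **Assumed, because not given:** schools per district (1, 2, 4, 5 or 10) and the form of the model.

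**Step 1. The plan's own figures.** The target here is the nominal 0.05; the last column of the table in step 3 shows that a school-level analysis meets it. The one result the plan derives from this ICC, 80% power, is not reproduced by a standard two-sided cluster calculation: 200/1.475 = 135.6 effective students per arm with d = 0.27 gives about 0.60. That is a separate matter and nothing below relies on it.

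**Step 2. Benchmark: clustering ignored altogether.** Design effect DE = 1 + (m − 1) × ICC; type I error = 2 × (1 − Φ(1.96/√DE)).
- m = 20: DE = 1 + 19 × 0.025 = 1.475; 1.96/√1.475 = 1.614; error 0.107.
- m = 25: DE = 1 + 24 × 0.025 = 1.6; 1.96/√1.6 = 1.549; error 0.121.
- m = 20 with ICC 0.01 or 0.05: error 0.072 or 0.160.

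This is not the model in the article, which does plan a clustering variable. It shows what is at risk if that variable fails to capture the school.

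**Step 3. Models that cluster on district.** Simulation under the null: 20 schools of 20 students, school ICC 0.025, continuous outcome, no baseline covariate, 2,000 runs per layout. The Monte Carlo standard error is √(0.05 × 0.95/2000) = 0.005 near 0.05 and √(0.10 × 0.90/2000) = 0.007 near 0.10. Each cell gives the type I error without, then with, an extra district-level ICC of 0.01.

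| Schools per district | Districts | District random intercept, normal reference | District-robust variance, t on (districts − 1) df | t-test on school means, 18 df |
|---|---|---|---|---|
| 1 | 20 | 0.068, 0.060 | 0.060, 0.057 | 0.054, 0.051 |
| 2 | 10 | 0.089, 0.113 | 0.053, 0.058 | 0.040, 0.053 |
| 4 | 5 | 0.114, 0.102 | 0.048, 0.061 | 0.059, 0.046 |
| 5 | 4 | 0.108, 0.107 | 0.051, 0.059 | 0.051, 0.049 |
| 10 | 2 | 0.112, 0.111 | 0.054, 0.045 | 0.056, 0.046 |

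With two or more schools per district, the district random intercept gives about 0.09 to 0.11. With one school per district it gives 0.06 to 0.07. The district-robust variance with a t reference stays at about 0.045 to 0.06 throughout, because schools nest in districts and that variance covers the school correlation. It does so with fewer than 20 clusters whenever districts are shared.

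**Step 4. The replacement.** The test on school means stays between 0.04 and 0.06. If arms happen to be balanced within districts of two schools, it gives 0.050, or 0.033 (conservative) when districts also differ, which is a reason to allow district as an added level. A robust variance clustered on school but without small-sample correction gives 0.07 to 0.09 in the five layouts of the table, so 20 clusters do call for a correction.

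**The case against.** The strongest reply is that *district* is a slip for *school*. The sentence treats districts as the units that carry the arm, every other section speaks of schools, and no district is recruited. With delivery across the state, each district might also supply only one school. In either case the fitted model would in effect cluster on the randomised unit and the defect would be one of terminology. That is possible, but the article does not settle it, and the sentence uses the wrong unit twice. If it is a slip, the correction is the same.

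The second reply concerns size, and it stands. A reader might infer that school correlation is certainly unmodelled and that the error is doubled or worse. The documents do not support that. The 10.7% benchmark belongs to an analysis that ignores clustering, which is not what is planned. The article fixes neither the estimator nor the number of schools per district, and two plausible cases show little or no inflation. Errors well above 0.11 need a larger ICC, larger clusters, or an uncorrected normal-reference robust variance with few districts; the article specifies no such analysis.

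Three further limits stand. The ICC was set for an obesity measure; metabolic syndrome is binary, positive youth development has no stated ICC, and the simulation had no baseline covariate, so inflation for the two actual primary outcomes is not shown directly. A reader might also infer that private schools have no district; the article says only that they take part. Finally, a condensed article may leave the choice of small-sample method to the analysis plan, so its absence is not a fault in itself.

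**Conclusion.** The contradiction is real and the clustering rule is wrong as written: the analysis names a unit that the trial neither recruits nor randomises, against its own allocation and its own school-level ICC.

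The consequence is conditional. The error of about 0.09 to 0.11 holds for two or more schools per district with a district random intercept as the only cluster term, at ICC 0.025 and 20 students per school. The range of about 0.045 to 0.07 holds for one school per district, or for a district-robust variance with a small-sample t reference. Which case applies cannot be told from the article. The need for correction does not depend on it, because naming the school keeps the analysis aligned with the allocation in every layout.

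**What to change.** In the Quantitative analysis section, replace *district* with *school* in both places: the units compared and the clustering variable. The primary models then cluster on the randomised school, through a school random intercept or a marginal model clustered on school. District may be added as a higher level; if it is, state how private schools are assigned to one. Use a small-sample method suited to 20 clusters, for example Kenward-Roger or between-within degrees of freedom for a mixed model, or a bias-corrected robust variance with a t reference on about 18 df for a marginal model. The choice can sit in the analysis plan.

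The cost is wording only, with no change to recruitment or data collection. Standard errors may become slightly larger.

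### Extra covariates in the primary model are to be picked by bivariate screening of the trial's own data with no fixed rule, and the randomisation block is not a named term

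*Protocol article*

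**What the plan says.** The Quantitative analysis section begins by announcing "univariate and bivariate statistics to determine the distribution of outcome measures and to identify relevant covariates". It then describes the model for the two primary outcomes. Treatment group is the main independent variable, with "baseline score as a covariate, post-intervention score is the outcome, and district is a clustering variable". To these it adds: "Other covariates (e.g., student sex), identified in the preliminary bivariate analyses, will also be included in the model".

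The section does not give the candidates, an entry threshold or the timing of the screen. It does not say whether covariates are screened against the outcome or against the arm, or whether the screen is blind to arm. Sex is only an example.

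The Randomization section says: "Randomization will occur in two blocks of ten schools, at an equal one-to-one ratio". The Design section says: "We will recruit two cohorts of schools", 20 schools in total. Neither block nor cohort is named in the model.

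**The concern.** In a randomised trial the covariates of the primary model should be settled before the outcome data are seen. Here arm, baseline score and a clustering variable are settled, but the remaining covariates are whatever a preliminary look at the trial data turns up. Two analysts following the text faithfully could arrive at different models, and the set may differ between the two primary outcomes. What is at stake is control of the false-positive rate and, for metabolic syndrome, what is being estimated. That outcome is dichotomous. If a logit link is used (the link is not stated), the adjusted odds ratio changes with the covariate set even when the arms are perfectly balanced.

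The block is the reverse case. It is known from the design and balanced across arms, yet the text does not commit to it. If outcomes differ between blocks, that variation stays in the error term.

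**Working it through.** **Inputs from the protocol.** 20 schools, two blocks of ten at 1:1 (so five schools per arm in each block); 20 students per school analysed; a standardised difference d of 0.27; and, from the Sample size section, "we set an alpha of 0.05 and estimated a within-school intraclass correlation coefficient of 0.025 to account for cluster effect".

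**Inputs assumed.** Two-sided test; continuous standardised outcome; eight candidate covariates; 5% entry threshold; covariate effects and baseline correlation; block differences of 0, 0.2 and 0.4 SD. The protocol gives none of these.

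**The plan's own power figure.** School-mean variance = 0.025 + 0.975/20 = 0.07375. SE of the difference = √(4 × 0.07375/20) = 0.121. Then 0.27/0.121 = 2.22, and power is about 60% by the normal approximation or 56% on 18 df. The stated 80% is not reproduced. This point does not rest on that figure, because it compares analyses with one another under the same assumptions.

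**Screening.** 1,500 trials were simulated per setting, with a school-level t-test after covariate adjustment. Monte Carlo error is about 0.6 points on type I error and 1.3 points on power. With equal blocks and no block term:

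| Extra covariates | Type I error | Power at d = 0.27 |
|---|---|---|
| Two named in advance | 5.3% | 65% |
| Those associated with the outcome, p < 0.05 | 5.4% | 65% |
| Those imbalanced between arms, p < 0.05 | 5.0% | 63% |
| Most favourable of four sets (none, outcome-screened, imbalance-screened, all eight) | 7.7% | 70% |

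No single fixed rule does measurable harm to the error rate. The freedom to move between rules does. With block differences of 0.2 and 0.4 SD and no block term, the most-favourable choice gave 5.0% and 2.3%, against 3.4% and 1.6% with named covariates. The excess is still there but is masked by the conservative test described next.

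**Block.** With five schools per arm in each block, a block shift adds the same amount to both arm means and cancels from a linear estimate. It does not cancel from the residual variance. For a difference D, each arm of ten schools gains 10 × (D/2)²/9 in its estimated school-mean variance: 0.0111 for D = 0.2 and 0.0444 for D = 0.4. An SE of 0.109 with the block fitted implies a school-mean variance of 0.109² × 20/4 = 0.0594. Without the block the expected SE is therefore:

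- D = 0.2: √(4 × (0.0594 + 0.0111)/20) = 0.119
- D = 0.4: √(4 × (0.0594 + 0.0444)/20) = 0.144

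The simulation agrees (SE and power from the d = 0.27 runs, type I error from the null runs):

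| Block difference | Mean SE, without / with block | Actual spread of estimate, either way | Type I error, without / with | Power, without / with |
|---|---|---|---|---|
| 0 | 0.110 / 0.110 | 0.11 | 5.3% / 5.0% | 65% / 65% |
| 0.2 SD | 0.119 / 0.109 | 0.11 | 3.4% / 4.5% | 59% / 64% |
| 0.4 SD | 0.143 / 0.109 | 0.11 | 1.6% / 4.7% | 41% / 63% |

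The reported SE is 9% too wide at 0.2 SD (0.119/0.109) and 31% too wide at 0.4 SD (0.143/0.109), while the estimate varies no more than before.

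**The case against.** The strongest reply is that an article condenses the full plan, so a covariate list may sit in a document not shown. That answers a silence, but the selection step is not a silence. The article states a procedure in which bivariate results decide what enters the primary model. The reply has more force for the block. The list of other covariates is open, so the block is unnamed rather than excluded, and that half stands mainly as part of the remedy.

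Four stronger readings are tempting, and the documents do not support them.

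- *The primary estimate becomes less precise.* With balanced blocks the true variance of a linear estimate is unchanged. Only the reported SE grows, and only if blocks differ. Screening by one fixed rule left the SE practically unchanged too.
- *Screening in itself inflates the false-positive rate.* One fixed rule did not. The 7.7% needs an analyst who picks the best of several models, which the text permits but does not describe.
- *Irrelevant covariates are likely to enter.* With ten irrelevant candidates at a 5% threshold, the chance that at least one enters is 1 − 0.95¹⁰ = 40%. The arithmetic is right, but neither the count nor the threshold is in the protocol, and entry is not the same as harm.
- *Block means cohort or school year.* This is a plausible inference from the Design and Randomization sections, but neither says so.

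It is also fair to object that baseline adjustment would absorb part of any stable block difference, and that SD-scale figures do not carry over directly to a dichotomous outcome. Both limits stand.

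**Conclusion.** The point holds in a limited form. The protocol fixes a data-driven selection step for the extra covariates of the primary model, with no rule that would make it reproducible. The demonstrated risk is modest: type I error up to about 7.7% under deliberate choice among four covariate sets with equal blocks, and near nominal under any one fixed rule tried. Leaving the block unnamed risks a conservative test and lost power, not a biased or noisier estimate. The loss runs from nothing, if blocks are alike, to about 22 points of power (63% − 41%) at an assumed 0.4 SD difference.

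These sizes rest on a continuous outcome, a school-level test, equal school sizes and the assumed inputs listed above. They illustrate positive youth development better than metabolic syndrome. The change is worth making because it is cheap and removes an avoidable question about the primary result.

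**What to change.** Delete the bivariate selection step from the Quantitative analysis section. State one model in advance for both primary outcomes: arm, baseline value of the outcome, randomisation block, and a short named list of covariates already collected, for example sex and either age or grade. Keep a clustering term; which unit it should be is a separate question. Present any data-driven adjustment as a labelled sensitivity analysis.

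The cost is one degree of freedom for the block (18 to 17 in a school-level test) and a few lines of wording. Sex, date of birth and grade are collected at baseline, and the block is known from the randomisation, so no new data are needed.

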#### Qualitative analysis

We will use a thematic approach, informed by the SHOWeD framework, to analyze photovoice data (64, 79). First, audio recordings of group discussions and structured observation notes from each phase (walkabout, picture selection, and discussion) will be transcribed verbatim and uploaded into qualitative data management software for coding. A team of trained researchers will independently review transcripts and observation rubrics, applying an inductive-deductive coding strategy. Deductive codes will be informed by the SHOWeD framework and the study's research objectives, while inductive coding will allow for emergent themes that reflect participants' unique perspectives on environmental challenges and facilitators. To ensure reliability, two researchers will code a subset of transcripts and reconcile discrepancies through discussion, refining the codebook iteratively. A comparative analysis will be conducted between photovoice session three and session 15 to examine changes in student-identified environmental barriers, facilitators, and perceived improvements over time. Key themes and representative quotes will be synthesized to capture students' perceptions of their school environment, and findings will be triangulated with observational data to provide a comprehensive understanding of how students perceive and experience environmental change throughout the program.

